***Quality of life evaluation***

Quality of live will be evaluated by the EQ-5D questioner[^72^](#_ENREF_72)^,^ [^73^](#_ENREF_73). EQ-5D essentially consists of 2 pages - the EQ-5D descriptive system and the EQ visual analogue scale (EQ VAS). The EQ-5D descriptive system comprises the following 5 dimensions: mobility, self-care, usual activities, pain/discomfort and anxiety/depression. Each dimension has 3 levels: no problems, some problems, extreme problems.

The EQ VAS records the respondent’s self-rated health on a vertical, visual analogue scale where the endpoints are labeled “Best imaginable health state” and “Worst imaginable health state” (0 is denoting the worst imaginable health state while 100 is denoting the best imaginable health state). The validity and reliability of the EQ­5D questionnaire have been tested[^74^](#_ENREF_74)^,^[^75^](#_ENREF_75).

The EQ-5D questioner is attached in appendix 3.

**Administration and regulation**

**Informed Consent**

The investigator will obtain written informed consent from the patient participates in this study after adequate explanation of the aims, methods, objectives, and potential hazards of the study and prior to undertaking any study-related procedures. The investigator must utilize a consent form for documenting written informed consent. Informed consent will be appropriately signed and dated by the patient or the subject’s legally authorized representative and the person obtaining consent.

**Confidentiality**

Subjects’ anonymity will be strictly maintained and that their identities are protected from unauthorized parties. The information is not to be disclosed to any third party (except for medical stuff or employees or agents directly involved in the conduct of the study or as required by law).

**Study Files**

The medical records will be maintained adequately to enable good data storage and latter on management. Subject clinical source documents would include (although not, limited to) the following: subject hospital/clinic/ hyperbaric unit records, physician’s and nurse’s notes, appointment book, original laboratory reports, electroencephalogram (EEG), X-ray, SPECTs, CT and special assessment reports, consultant letters, screening and enrollment log etc.

**Statistical Considerations**

## Analysis Sets

### Safety Analysis Set

The safety analysis set will consist of all subjects for whom the study treatment was initiated.

### Primary Efficacy Analysis Set

In this trial will be measured the co-primary endpoint parameters: *improvement in NIHSS tests score* and *improvement in ADL score* following HBOT treatment for post stroke patients suffering chronic neurological deficiencies.

The primary efficacy analysis evaluation will include all subjects who completed the HBOT treatment or the control period; had no major protocol violations, and for whom there is a valid *NIHSS and ADL tests score* following 2 months of HBOT treatment.

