**Exclusion criteria**

Patients will be excluded if they will have one of the following criteria:

- Dynamic neurologic improvement or worsening during the last month
- Had been treated with HBOT for any other reason prior to their inclusion
- Have any other indication for HBOT;
- Chest pathology incompatible with pressure changes;
- Inner ear disease;
- Patients suffering from claustrophobia;
- Inability to sign written informed consent.
- Smoking patients were not allowed to smoke during the study and if they could not comply with this demand they were excluded.
- Inability to sign informed consent

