***Study protocol***

After signing the informed consent, patients were randomized in 1:1 manner into the treated or the control-cross group. After the randomization, patients were invited for baseline evaluation that included full review of their medical status and complete physical examination. All patients had baseline CT scan. After their inclusion patients were randomized to two groups: a treated group and a cross group. All patients had evaluation of their neurologic functions by physical examination, ability to perform activities of daily living, quality of life and brain functional imaging (rCBF-SPECT scan). The patients in the treated group were evaluated twice – at baseline and after 2 months of HBOT treatment. The patients of the cross group were evaluated three times – at baseline, after a 2 month control period of no treatment and after a consequent 2 month period of HBOT treatment. We emphasize that the study was a cross-over trial and patients in the cross group received HBOT treatment after their second evaluation and had a third neurological evaluation after the cross, when they have completed their HBOT.

The following HBOT treatment protocol was practice: The patient were treated 40 times (each treatment session was given on a separate day) distributed over two months (five days a week). Each session was for 90 minutes in 100% oxygen atmosphere and at pressure of 2 ATA.

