### Primary Efficacy Analysis

This study has co-primary endpoints: *NIHSS tests score* and *ADL score.* For each of the co-primary endpoints we will compute Overall Proportion of Success:

The following hypotheses are specified and will be tested separately:

For *NIHSS tests score* proportion of improvement:

H_0_: p_1_< p _2_

H_1_: p _1_> p _2_

While p1= 0.25 and p2=0.04

For *ADL score* proportion of improvement:

H_0_: p_1_< p _2_

H_1_: p _1_> p _2_

While p1= 0.25 and p2=0.04

Each of these hypotheses will be tested by:

1. Constructing a one-sided, lower 95% confidence interval about the observed Overall Proportion of Success in the relevant cohort.
2. Examining whether the lower limit of the confidence interval is at or above the success criterion

Study success will be declared if the following is met:

1. Lower confidence limit of HBOT treatment success is at 0.25 or above

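### The primary efficacy set admits only violation-free completers with a post-HBOT score, so the success proportion can be inflated, and its entry rule contradicts itself for the cross group

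*Protocol*

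**What the plan says.** The protocol section Primary Efficacy Analysis Set sets three conditions. The set "will include all subjects who completed the HBOT treatment or the control period; had no major protocol violations", and subjects must also have valid NIHSS and ADL scores "following 2 months of HBOT treatment".

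The only other set is for safety: "The safety analysis set will consist of all subjects for whom the study treatment was initiated". No efficacy set of all randomised patients is stated, and no rule says how a patient who does not complete is counted.

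Under Study protocol, "patients were randomized in 1:1 manner into the treated or the control-cross group". The treated group receives 40 sessions of 90 minutes, five days a week over two months. The cross group has two months without treatment and then the same course. NIHSS is scheduled at baseline and month 2 for everyone, with a third evaluation at month 4 for the cross group only.

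The Randomization section states that patients knew their arm, that ADL was unblinded, and that a fully blinded NIHSS could not be assured.

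Under Primary Efficacy Analysis the rates are given as "While p1= 0.25 and p2=0.04". Study success is declared when the one-sided 95% lower limit for the success proportion is at least 0.25.

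**The concern.** Finishing treatment, avoiding a major violation and having a score after HBOT are all settled after randomisation, and each may be related to outcome. A patient who stops HBOT because of intolerance, worsening or burden leaves the denominator instead of counting as not improved. The hurdle also differs by arm: a long course of chamber sessions against a waiting period. Major violation is not defined in that section, and in an open-label trial it can be judged with the allocation, and possibly the outcome, known.

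The sentence has a second defect. It admits patients who completed the control period, but also asks for a score after HBOT. A cross-group patient has no such score until month 4. On one reading, a control patient with complete month-2 data is lost if the later HBOT course is not finished. On the other, the month-2 score is enough. The text supports both, and they give different control groups.

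This set decides whether the study is declared a success.

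**Working it through.** **Inputs from the protocol.** Rates 0.25 and 0.04, N = 31, 80% power, one-sided alpha 0.05 with a normal approximation (Sample Size Considerations; Primary Efficacy Analysis). Success rule: one-sided 95% lower limit at or above 0.25.

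**Assumptions, because the protocol gives no figure.** d is the share of patients excluded, and q is the success rate among them. Each calculation concerns one endpoint.

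**1. The stated N.** The unpooled two-sample normal approximation gives (1.645 + 0.842)² × (0.25×0.75 + 0.04×0.96) / 0.21² = 31.67 per arm. The stated 31 is therefore close to a per-arm figure, although the protocol does not say whether it is per arm or total. I use 31 as the working denominator.

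**2. How many added failures reverse a pass.** The lower limit is x/n − 1.645 × √[(x/n)(1 − x/n)/n]; the exact binomial limit is alongside. Here 31 patients are in the set and further excluded patients are added back as failures.

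| Successes / patients | Normal limit | Exact limit | Rule |
|---|---|---|---|
| 12/31 | 0.243 | 0.241 | fails |
| 13/31 | 0.274 | 0.269 | passes |
| 13/33 | 0.254 | 0.251 | passes |
| 13/34 | 0.245 | 0.243 | fails |
| 14/36 | 0.255 | 0.253 | passes |
| 14/37 | 0.247 | 0.245 | fails |
| 15/39 | 0.257 | 0.254 | passes |
| 15/40 | 0.249 | 0.247 | fails |

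Thirteen is the smallest passing count out of 31. It takes 3 added failures to reverse 13/31, 6 to reverse 14/31 and 9 to reverse 15/31.

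**3. Chance of passing.** Let 31 be randomised with a true success rate of 0.25 over all of them. The completers' rate is (0.25 − d×q)/(1 − d). The chance of passing is the binomial probability of at least r successes among the completers, where r is the smallest count meeting the rule.

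| d | Completers | r | Rate, q = 0 | Chance, q = 0 | Rate, q = 0.04 | Chance, q = 0.04 | Chance, q = 0.25 |
|---|---|---|---|---|---|---|---|
| 0 | 31 | 13 | 0.250 | 2.9% | 0.250 | 2.9% | 2.9% |
| 10% | 28 | 12 | 0.278 | 6.2% | 0.273 | 5.6% | 2.9% |
| 20% | 25 | 11 | 0.313 | 12.4% | 0.303 | 10.3% | 3.0% |
| 30% | 22 | 10 | 0.357 | 23.0% | 0.340 | 18.1% | 3.0% |

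With q = 0.25 the completers' rate stays at 0.25 whatever the exclusion. With q = 0 the chance of passing at a true rate of 0.25 is above the stated one-sided 5% already at 10% exclusion.

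**The case against.** Several stronger readings are tempting, and the case against them is sound.

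- **That the set does inflate the success rate.** The protocol gives neither a dropout rate nor outcomes among those excluded. Inflation needs excluded patients to do worse than completers. That is plausible for patients leaving through intolerance or worsening, but it is not shown.
- **That three patients decide the result.** This is true only at the minimum passing count, and only if all three are failures. One or two more successes raise the number to six or nine.
- **That a between-arm bias in favour of HBOT is demonstrated.** The declaration rule sets one proportion, in an undefined relevant cohort, against 0.25 and uses no contrast between arms. In a comparison, dropping control non-completers could raise the control rate too. However, removing failures from the denominator acts directly on the single proportion, so the concern does not depend on a comparison.
- **That control patients who do not finish the later HBOT course are definitely removed.** This is one reading of a sentence that also admits completion of the control period. The text establishes a contradiction, not a settled rule.
- **That the smoking clause removes more patients from the chamber arm.** The eligibility list says of smokers that "if they could not comply with this demand they were excluded". It does not say whether this means non-enrolment, withdrawal or removal from analysis, and nothing indicates that smoking would be noticed more in one arm.

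One could add that the 25% target is presented as grounds for further investigation, so the trial is partly exploratory, and that an analysis plan might define an all-randomised set. The first softens the consequence. The second does not answer the point, since the protocol itself fixes which set is primary.

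**Conclusion.** The point stands in conditional form. The protocol makes a completer set, free of major violations, its primary efficacy set, and no all-randomised efficacy set is stated beside it. In an open-label randomised trial with unequal completion hurdles, that rule can yield a wrong declaration of success. The entry condition for the cross group is also contradictory and must be reconciled.

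The size depends on assumptions about exclusions. The step from 2.9% to 23% at 30% exclusion is the extreme case, with every excluded patient a failure. If they succeed at 4%, the figure is about 18%; if they succeed as often as completers, the chance stays near 3%. The documents cannot say which applies, and the present rule gives no protection if the unfavourable case is the true one.

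**What to change.** - Define the primary efficacy set as all randomised patients, analysed in the arm to which they were randomised, on the month-2 NIHSS and ADL.
- Seek the month-2 assessment whether or not all sessions were completed.
- Count a missing outcome as not improved in the proportion-of-success analysis, and report the number missing by arm.
- For the between-arm analysis, require only the month-2 score from cross-group patients. Reword the sentence so that completion of the control period and the post-HBOT score no longer conflict.
- Keep the present definition as a per-protocol sensitivity set.

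The cost is mostly wording, since the month-2 evaluation is already scheduled for all patients. It does need some effort to bring back patients who stop treatment, and the success rate may look less favourable.

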**Sample Size Considerations**

Presentation of sample size is based on achieving 80% power overall to demonstrate that improvement rate in *NIHSS test score* is at least 0.25 and, separately, that improvement rate in *ADL test score* is at least 0.25. An improvement rate of at least 25% in the NIHSS test and ADL score in the treatment group (comparing to baseline, prior to HBOT treatment) would be an appropriate clinical target for HBOT treatment success and of sufficient interest to encourage further investigation of HBOT treatment for post stroke patients suffering chronic NIHSS deficiencies.

Sample size was based on the assumption that exposure to the NIHSS tests and ADL evaluation (at baseline) without any additional training might induce up to 4% score improvement in the second NIHSS test (following treatment). Assuming a true success rate of 25% a sample of N = 31 will provide 80% power to show that HBOT treatment induces at least 25% improvement on *NIHSS test score* and separately, on *ADL test score*. This is based on a power analysis using the normal approximation for the binomial, with one-sided Alpha=0.05.

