**Activities of daily living (ADL)**

The activities of daily living (ADL) will be evaluated by a questioner that covers the following functions: bathing, dressing, grooming, oral care, toileting, walking, climbing stairs, eating, shopping, cooking, managing medications, using phone, housework, doing laundry, driving and managing finances[^71^](#_ENREF_71). For each criterion the patient had to define whether he/she is independent, needs help, dependent or does not do at all (The range of the total score is from 0 (best) to 51 (worst)).

The ADL is attached in appendix 2.

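### The 25% target and the 4% practice effect are stated as changes in score but used as proportions of patients, so the power claimed at N = 31 has no support

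*Protocol*

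**What the plan says.** Sample Size Considerations gives the target as "An improvement rate of at least 25% in the NIHSS test and ADL score in the treatment group", measured against the baseline before HBOT, and the gain expected without treatment as repeat testing that "might induce up to 4% score improvement in the second NIHSS test (following treatment"). Each is worded as a percent change in a score.

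The same section then treats 25% as a rate of success: "Assuming a true success rate of 25% a sample of N = 31 will provide 80% power". It says that this rests on a normal approximation to the binomial, "with one-sided Alpha=0.05".

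Primary Efficacy Analysis continues in that second sense: "For each of the co-primary endpoints we will compute Overall Proportion of Success". For NIHSS and ADL alike it sets p1 = 0.25 and p2 = 0.04, and it declares success if the lower one-sided 95% confidence limit for the success proportion is 0.25 or higher. No section states what change in NIHSS or ADL makes a single patient a success.

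**The concern.** A binomial proportion counts patients; a percent change in score describes how far a score moves. The two are linked only through a per-patient threshold and the spread of individual changes, and the protocol gives neither. The 4% enters as an assumed practice effect on the score and reappears as the share of patients who succeed without treatment, with nothing in between.

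Sample size, hypotheses and success rule all rest on p1 and p2. If 0.04 is not a supported untreated responder rate, the stated 80% power is not supported either, and a result compared with 0.04 cannot be read as an effect beyond what untreated patients show. The trial has a randomized control arm that could supply this rate, but the stated hypotheses use a constant.

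**Working it through.** **Inputs from the protocol.** One-sided alpha 0.05, power 80%, N = 31, p1 = 0.25, p2 = 0.04, success rule with lower limit at or above 0.25, allocation 1:1. The text does not say whether 31 is per arm or in total.

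**1. Reproducing N = 31.** Two independent proportions, unpooled variance, one-sided:

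n per arm = (z0.95 + z0.80)² × [p1(1 − p1) + p2(1 − p2)] / (p1 − p2)²
= 6.1826 × (0.1875 + 0.0384) / 0.21²
= 6.1826 × 0.2259 / 0.0441 = 31.67.

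Power at 31 per arm is Φ(0.21 / √(0.2259/31) − 1.645) = Φ(2.460 − 1.645) = 79.3%. A two-sample arcsine formula gives 30 per arm. The pooled version gives 34, and the one-sample normal approximation gives 11 (16 with continuity correction). The stated figure therefore fits a two-sample calculation in which 0.04 is the share of patients who succeed in a comparison group. The arithmetic is sound on its inputs; the fault is in what the inputs mean.

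**2. What a 4% mean gain implies for responders.** The documents give no SD and no responder threshold. Assumptions: percent change in untreated patients is normal with mean 4%, and a responder improves by at least 25%. The rate is then 1 − Φ((25 − 4)/SD):

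| Assumed SD (points) | Untreated responder rate |
|---|---|
| 10 | 1.8% |
| 15 | 8.1% |
| 20 | 14.7% |
| 25 | 20.0% |
| 30 | 24.2% |

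The error can go either way. Suppose every patient has baseline NIHSS 4 and only one-point gains occur. A 4% mean gain is 0.04 × 4 = 0.16 points, so 16% of patients gain a point, and each of them has improved by 25%. With baseline 10, 4% is 0.4 points, a one-point gain is 10%, and nobody reaches 25%.

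**3. Effect on power.** Same formula, p1 = 0.25, 31 per arm:

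| Untreated rate p2 | Power at 31 per arm | n per arm for 80% |
|---|---|---|
| 0.018 | 89% | 24 |
| 0.04 | 79% | 32 |
| 0.081 | 58% | 57 |
| 0.10 | 48% | 77 |
| 0.16 | 22% | 246 |
| 0.20 | 12% | 860 |

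**4. The success rule.** The lower one-sided 95% limit must be at least 0.25 with n = 31:

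- 12 of 31: Wilson 0.258, Wald 0.243, Clopper-Pearson 0.241.
- 13 of 31: Wilson 0.286, Wald 0.274, Clopper-Pearson 0.269.

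So 12 successes suffice with Wilson limits and 13 are needed with the other two. At a true rate of 0.25, P(X ≥ 12) = 6.4% and P(X ≥ 13) = 2.9%, against the 80% stated.

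**The case against.** The wording can be read as a responder analysis with a loose sentence about the 4%. The terms used in the hypotheses and in the power statement all point to counting patients, and a statistical analysis plan that is not shown may define the responder. That is fair as far as the definition goes. It does not remove the contradiction, because the protocol itself describes the 4% as a gain in score and then fixes it as p2.

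Nor is it right that the protocol has no reference value. It states two, 0.04 and 0.25. The complaint is that neither is justified as a responder rate and that they disagree with each other.

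A reader might infer that 0.04 understates the untreated rate and that false positives are therefore frequent. With an untreated rate of 0.16, for example, a rule of 4 or more successes in 31 would be met 75% of the time. The documents do not support this. That cut-off comes from a one-sample test against 0.04, which is not the rule written for declaring success. Under the written rule, a true rate of 0.16 gives success at most 0.2% of the time (P(X ≥ 12) = 0.0020). The direction of the error is also unknown: the range in the first table starts below 0.04, and no baseline NIHSS distribution is given.

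Finally, abandoning the dichotomy is not the only remedy. A defined responder with a concurrent comparator also cures the fault.

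**Conclusion.** The point stands as an error in the protocol's own text: percent changes in score are used as proportions of patients, and no per-patient success is defined. The stated 80% power at N = 31 holds only if 4% of untreated patients would succeed, which nothing in the protocol supports. Under the assumed normal model with SD 10 to 30, the untreated rate is about 2% to 24%. Power at 31 per arm is 79% at 0.04, 48% at 0.10 and 22% at 0.16. These figures rest on the assumed SDs, an assumed 25% threshold, p1 held at 0.25, and 31 read as a per-arm number. They show how sensitive the claim is; they do not estimate the true rate.

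The conflict between 0.04 and 0.25 does not depend on the SD or threshold assumptions. The written rule succeeds about 3% to 6% of the time at the rate for which 80% power is claimed. Because hypotheses, sample size and success rule all use these two constants, this needs correcting before the primary result can be interpreted.

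**What to change.** Make the primary comparison treated versus control at 2 months, separately for NIHSS and ADL. Both arms are already assessed at baseline and at 2 months, so no new data are needed. Choose one of two forms:

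- Baseline-adjusted scores compared between arms.
- A responder defined for each patient, for example at least 25% improvement from the patient's own baseline, with the control arm's observed rate as comparator in place of 0.04.

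Replace the success rule with one that matches the chosen comparison. Restate the sample-size paragraph on the same scale, say whether N is per arm or in total, and give the untreated rate or the SD as an assumption with a range.

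The cost is a protocol amendment and a new power calculation. The continuous form needs SDs that the protocol does not give. Since randomization is described in the past tense, the change should be dated relative to any look at outcome data, and the power may have to be reported for the number already recruited.

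A separate, minor check: the ADL section lists 16 functions with four response categories but states "The range of the total score is from 0 (best) to 51 (worst"). If items are scored 0 to 3, which is inferred, the maximum is 16 × 3 = 48, and 51 would need 51 / 3 = 17 items. The questionnaire appendix is not shown and may settle this. It has no bearing on p1, p2 or N.

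### The stated 80% power at N = 31 belongs to no test in the primary efficacy analysis: the 0.25 success limit equals the assumed true rate, it conflicts with the 0.04 in the hypotheses, and N is not labelled

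*Protocol*

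**What the plan says.** **Protocol, Sample Size Considerations.** The aim is given as "Presentation of sample size is based on achieving 80% power overall" for NIHSS and, separately, for ADL. The inputs are "Assuming a true success rate of 25" per cent, a retest effect that "might induce up to 4% score improvement in the second NIHSS test", and a test "with one-sided Alpha=0.05". From these the section concludes that "a sample of N = 31 will provide 80% power". The method is described only in these words: "This is based on a power analysis using the normal approximation for the binomial". Nothing says whether it is a one-sample or a two-sample calculation, or whether 31 counts patients per arm, in total or receiving HBOT.

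**Protocol, Primary Efficacy Analysis.** For each endpoint the hypotheses set p1 against p2, with p1 fixed at 0.25 and p2 at 0.04. The test steps then use a single observed proportion: compute its one-sided lower 95% confidence limit and compare that limit with a criterion. The criterion for study success is "Lower confidence limit of HBOT treatment success is at 0.25 or above".

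**Protocol, Study protocol.** The design is randomised: "patients were randomized in 1:1 manner into the treated or the control-cross group". The primary analysis contains no step that compares the observed proportions of the two groups.

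**The concern.** Four items have to agree: the assumed true rate, the bound to be beaten, the number of patients and the power. Here the assumed true rate (0.25) is also the bound that the lower confidence limit must reach. A lower 95% limit lies at or above the true value only about one time in twenty, so such a rule cannot have 80% power at that rate.

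The hypotheses in the same section name a different bound, 0.04. Whoever runs the analysis must therefore choose between two criteria that give nearly opposite chances of success. Applied as written, the 0.25 rule would declare failure on each endpoint about 94% to 97% of the time if HBOT works exactly as the protocol assumes. A move to 0.04, or to a comparison with control, after the data are seen would be an unplanned change of the primary analysis. With N unlabelled, a reader also cannot tell how many patients the stated power refers to.

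**Working it through.** **Inputs, all from the protocol.** True rate p1 = 0.25; reference rate p2 = 0.04; one-sided alpha 0.05 (z = 1.645); power 0.80 (z = 0.842); N = 31; success limit 0.25. Both rates are read as proportions of patients who improve, as the hypotheses read them.

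**1. Can 31 be reproduced?**

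*One sample against 0.04:* n = [(1.645·√(0.04·0.96) + 0.842·√(0.25·0.75)) / 0.21]² = 10.7, so 11. With continuity correction it is 15.1, and by the arcsine form 14.9. None of the one-sample variants tried gives 31.

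*Two samples, 0.25 against 0.04, per arm:*
- unpooled variance: (1.645 + 0.842)²·(0.1875 + 0.0384) / 0.21² = 31.7
- pooled variance under the null (mean rate 0.145): [1.645·√(2·0.145·0.855) + 0.842·√(0.1875 + 0.0384)]² / 0.21² = 33.7
- arcsine: 29.8

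So 31 is close to a two-sample per-arm size. Rounded up, however, these give 32, 34 and 30, and none is exactly 31.

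**2. Power of the stated success rule (lower limit at or above 0.25) with n = 31.** First find the smallest number of successes that meets the rule, then its exact binomial probability.

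| Limit | At 12/31 | At 13/31 | Needed | Power at true rate 0.25 | True rate for 80% |
|---|---|---|---|---|---|
| Wald | 0.243 | 0.274 | 13 | 2.9% | about 0.48 |
| Clopper-Pearson | 0.241 | 0.269 | 13 | 2.9% | about 0.48 |
| Wilson | 0.258 | 0.286 | 12 | 6.4% | about 0.45 |

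More patients do not help. At n = 62 all three limits need 22 successes, with power 4.3%. At n = 100 power is 4.5%, and at n = 10,000 it is 5.0%.

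**3. Power against 0.04 with n = 31, one sample.** The normal approximation gives Φ[(0.21 − 1.645·√(0.0384/31)) / √(0.1875/31)] = Φ[(0.21 − 1.645·0.0352) / 0.0778] = 97.5%. In exact terms, a Wilson or Clopper-Pearson limit at or above 0.04 needs 4 of 31, with power 96.9%. A Wald limit needs 5 of 31, with power 91.7%.

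**4. If a randomised comparison at month 2 was intended.**
- 31 per arm: 76.9% (pooled) to 79.3% (unpooled) by the normal formula.
- 31 in total, taken as 15.5 per arm: 50.6% (pooled) to 53.8% (unpooled).

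At a 4% control rate only 31·0.04 = 1.2 control successes are expected, so the normal formula is fragile. Exact enumeration at 31 per arm gives 83% for the pooled z-test and 65% for a one-sided Fisher test.

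**5. Two endpoints.** The figures in steps 2 to 4 are per endpoint. If both endpoints must succeed and are taken as independent (an assumption; the protocol states neither), the 76.9% to 79.3% becomes 0.769² = 59% to 0.793² = 63% jointly.

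**The case against.** The protocol names only a normal approximation for the binomial, not a two-sample formula, so the origin of 31 is a guess. The hypotheses are also written as p1 against p2, the notation of a two-group comparison, and the trial has a randomised untreated control period. Finally, if the working bound is 0.04, then 80% understates the power, and an understatement puts no one at risk.

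Most of this stands. A reader might infer from the near match in step 1 that 31 is a per-arm number, that 62 patients are planned, and that the trial was sized for a comparison that the plan never contemplates. The documents do not support that. Neither 62 nor a per-arm label appears anywhere, no formula tried rounds up to 31, and the p1-against-p2 notation leaves open that a comparison was in mind. The sample size section also describes the target as change from baseline in the treatment group, and both groups eventually receive HBOT. So 31 could equally mean the treated group or everyone who receives HBOT.

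It is also true that only the 0.25 rule harms the trial. But that rule is the one stated criterion for study success, and the notation does not rescue it: p2 is a fixed 0.04 and the test steps use one proportion. The contradiction does not depend on where 31 came from.

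**Conclusion.** The point holds. At the assumed rate of 0.25 with 31 patients, the success rule as written has about 3% to 6% power, and a one-sample test against the 0.04 in the hypotheses has about 92% to 97%. The stated 80% matches neither. The primary efficacy section conflicts with itself (0.04 against 0.25) and with the sample size section, and N carries no label.

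The two errors differ in weight. The 0.25 limit makes success improbable under the protocol's own assumption at any sample size. The mismatch against 0.04 only understates the power. That 31 was meant for a treated-versus-control comparison is suggested by the arithmetic and not proved by it.

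The ranges reflect the choice of confidence limit, which the protocol does not name. All figures are per endpoint, assume 31 evaluable patients, and treat success as a yes/no outcome for each patient.

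**What to change.** 1. Remove the requirement that the lower limit reach 0.25, and use one bound or comparator that agrees with both the hypotheses and the sample size. Alternatively keep it, and state that its power at a true rate of 0.25 is about 3% to 6%.
2. State whether 31 is per arm, the total or the number treated. Only the sponsor can say which was meant.
3. Restate the power for the test that is kept:
   - one sample against 0.04 with 31 patients: about 92% to 97%;
   - randomised month-2 comparison, if made primary: about 77% to 79% by the normal formula with 31 per arm, or about 51% to 54% if 31 is the total, with the test named because exact power depends on it.
4. Say that these figures are per endpoint. If both co-primary endpoints must succeed, they are not the overall 80% that the protocol promises.

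**Cost.** This is more than rewording, because it amends the primary success criterion and, if the randomised comparison is chosen, the primary test. The stated power may become less favourable. No extra patients are required to make the plan consistent.
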